### Measurements

Baseline characteristics, including gender, age, body height and weight, abdominal circumference, complications, duration of T2DM, background treatment, and smoking and drinking habits will be recorded prior to randomization. The status of the study medications and the participant’s background treatment will be recorded at each visit. Measurements of BP, pulse rate, BW, and body mass index (BMI) will also be carried out at baseline and after 12 and 24 months. Abdominal circumference will be measured at baseline and 24 months. Blood tests without HbA1c level will be checked at baseline and 24 months (details listed in Additional file 2); HbA1c will be measured at baseline and after 12 and 24 months. Specific biomarkers such as N-terminal pro-brain natriuretic peptide (NT-proBNP), high-sensitivity C reactive protein (hsCRP), high-molecular weight adiponectin, and malondialdehyde modified low-density lipoprotein (MDA-LDL) will be measured at baseline and 24 months. Creatinine-corrected urinary albumin excretion will be measured at baseline and 24 months (optional). Some optional imaging and physiological tests are also planned in the study including abdominal computed tomography to measure the amount of visceral and subcutaneous fat, echocardiograms, flow-mediated dilation (FMD), pulse-wave velocity (PWV), cardio-ankle vascular index (CAVI), and augmentation index (AI) (details listed in Additional file 3).

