#### Measurement of carotid IMT

The protocol and method for measuring carotid IMT have been described in detail previously [25, 31, 32]. In brief, the carotid ultrasound examinations using standardized imaging protocols and systems equipped with >7.5 MHz linear transducers will be performed at each local site and then measured at a core laboratory (Tsukuba University) at baseline and 24 months after randomization. Expert trained sonographers who have attended a lecture on measuring carotid IMT will carry out the procedure according to the Mannheim carotid IMT consensus [33, 34]. The head position and probe angle of the ultrasound approach will be set using a ruler located just cephalad (Fig. 2). Longitudinal B-mode images, perpendicular to the ultrasound beam, with a 3–4 cm imaging depth, will be recorded in the distal common carotid arteries (CCA), carotid bulbs, and proximal internal carotid arteries (ICA) on both sides. The lateral probe incidence is used to obtain CCA images, using external landmarks and an original semicircular protractor developed for this purpose. The mean CCA-IMT indicates the average IMT value of the right and left CCA-IMT, 10 mm from the bulb. The following far wall IMTs will be measured; maximum IMT of the CCA and mean and maximum IMTs of the bulb and ICA. The optimized R-wave gated still frames of the carotid IMT will be stored as JPEG files, with all the parameters collected and measured at the core laboratory. An expert analyzer blinded to the allocation and clinical information of the subjects will measure all the IMT values using an automatic IMT measurement software program (Vascular Research Tools 5, Medical Imaging Applications, Iowa, USA) [35]. The software program identifies the lumen/intima and the media/adventitia borders in this region and calculates the distance between them.

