### Study endpoints

Intima-media thickness (IMT) in the carotid artery is well-established as a surrogate marker for risk of CV diseases and is also useful for evaluating the effectiveness of various types of therapeutic interventions in patients with or without T2DM [35–37]. The primary endpoint in the study is the change in mean IMT of the CCA from baseline to 24 months. The secondary endpoints are the values and changes in parameters after 24 months of treatment, including: (1) mean IMT of the bulb and ICA, (2) max IMT of the CCA, bulb, and ICA, (3) the overall mean of mean IMT of the CCA, bulb, and ICA, (4) the mean of max IMT of the CCA, bulb, and ICA, (5) specific biomarkers including hsCRP, MDA-LDL, NT-proBNP, and high-molecular weight adiponectin, (6) the cardiovascular functional tests listed in Additional file 3 (optional), (7) abdominal circumference and amount of visceral and subcutaneous fat measured by abdominal computed tomography (optional), (8) creatinine-corrected urinary albumin excretion. In addition, the values and changes after 12 and 24 months in several clinical parameters including BP, BW, and BMI and laboratory data (details listed in Additional file 2) will be evaluated. Safety endpoints also include AEs and adverse drug reactions observed during the study.

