#### Statistical analysis plan

The analyses of the primary and secondary endpoints will be performed in the full analysis set (FAS), which includes all participants who received at least one dose of treatment during the study period and did not have any serious violation of the study protocol such as not providing informed consent, registration outside of the study period, or data collected after commencement of treatment.

Summary statistics will be calculated for the baseline characteristics including the frequencies and proportions for categorical variables and means ± standard deviations for continuous variables. The patient characteristics will be compared using Chi square tests for categorical variables, t tests for normally distributed continuous variables, or the Wilcoxon rank sum tests for continuous variables with a skewed distribution.

The analysis plan is similar to that used in previous studies we have conducted [25, 31, 32]. In brief, for the primary analysis comparing treatment effects, the baseline-adjusted means and their 95 % confidence intervals, estimated by analysis of covariance of the change in average carotid IMT at 24 months, will be compared between the treatment groups (ipragliflozin group vs. control group). The results will be adjusted by allocation factors. The primary analysis will not include missing observations, with the mixed effects model for repeated measures (MMRM) being used as a sensitivity analysis to examine the effect of missing data. In addition, MMRM will be used as a sensitivity analysis to examine the outcomes at baseline and 24 months modelled as a function of time, treatment, and treatment-by-time interaction. The secondary analysis will be performed in the same manner as the primary analysis.

All comparisons are planned and all *P* values will be two sided. *P* values <0.05 will be considered statistically significant. All statistical analyses will be performed using SAS software version 9.4 (SAS Institute, Cary, NC, USA). The statistical analysis plan will be developed by the principal investigator and a biostatistician before completion of patient recruitment and database lock.

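### Variables measured at both 12 and 24 months are compared at 24 months by a complete-case ANCOVA that makes no use of the 12-month value (minor)

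*Protocol article*

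**What the plan says.** All references are to the protocol article.

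- **Primary method** (Statistical analysis plan): a baseline-adjusted ANCOVA of the 24-month change in carotid IMT, also adjusted for the allocation factors. On missing data: "The primary analysis will not include missing observations".
- **MMRM** (same section): a sensitivity analysis only, mentioned twice. The first mention concerns the effect of missing data and names no visits. The second is "to examine the outcomes at baseline and 24 months modelled as a function of time, treatment, and treatment-by-time interaction".
- **Secondary analysis** (same section): "The secondary analysis will be performed in the same manner as the primary analysis". No other method is given for any secondary variable.
- **IMT visits** (Measurement of carotid IMT): "measured at a core laboratory (Tsukuba University) at baseline and 24 months after randomization".
- **Visits for the other variables** (Measurements): "Measurements of BP, pulse rate, BW, and body mass index (BMI) will also be carried out at baseline and after 12 and 24 months", and "HbA1c will be measured at baseline and after 12 and 24 months".
- **Use of the 12-month values** (Study endpoints): after the numbered list of secondary endpoints, a further sentence says that the trial will also evaluate "the values and changes after 12 and 24 months in several clinical parameters including BP, BW, and BMI and laboratory data".

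**The concern.** For IMT, an analysis of participants with a 24-month value loses no follow-up information, because there is no earlier follow-up value. For HbA1c, blood pressure, pulse rate, body weight and BMI there is one. Carrying the IMT rule over to them has two effects on the main 24-month comparison. A participant with a 12-month but no 24-month value contributes nothing, and the 12-month result cannot help to account for who is missing later.

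The second effect matters more. In an open-label trial, participants doing badly at 12 months may leave more often, and more of them may be controls. A complete-case ANCOVA would then lose the worst control values and understate the treatment difference.

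Glycaemic improvement is part of the hypothesis in the Study overview. The Discussion expects an effect on atherosclerosis that is partly independent of glycaemic control. An understated HbA1c difference would make any IMT effect look somewhat more independent of glucose than it is.

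**Working it through.** **1. Visits and method side by side.**

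| Variable | Follow-up values | Used in the main 24-month comparison |
|---|---|---|
| Mean CCA-IMT | 24 months | 24 months |
| HbA1c, BP, pulse rate, BW, BMI | 12 and 24 months | 24 months only |

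The MMRM with stated time points covers baseline and 24 months. It can allow for loss that depends on baseline, which the ANCOVA already conditions on. Without the 12-month value it cannot allow for loss that depends on that value.

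**2. The plan's own figures.** The plan gives no effect size, SD or loss rate for these variables. The nearest figures are those for IMT: difference 0.016 mm, SD 0.06 mm, 5% two-sided, 80% power. Then n = 2 x (1.960 + 0.842)^2 x 0.06^2 / 0.016^2 = 221 per arm, or 222 with the t distribution, as stated. With 5% loss, 222 / 0.95 = 234. The planned 240 tolerates 1 - 222/240 = 7.5%. So 5% to 7.5% is the loss the trial was sized for. These figures are not disputed.

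**3. Form of the bias.** Let e12 and e24 be the 12- and 24-month residuals after arm and baseline, with equal SDs and correlation rho. If loss after month 12 depends only on the 12-month value, then

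bias of complete-case ANCOVA = rho x D,

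where D is the mean e12 of retained ipragliflozin participants minus that of retained controls. Under purely random loss D = 0. If high values leave more often and controls have more of them, D > 0, and a negative difference moves toward zero.

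**4. Illustration for HbA1c (all inputs assumed).** 240 per arm, true difference -0.30, residual SD 0.8, rho = 0.7. The log-odds of loss after month 12 rise by 0.7 to 1.8 per 1% HbA1c. The top value is an odds ratio of exp(1.8) = 6.0.

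- *About 4-7% total loss:* bias about 0 to 0.015. A bias of 0.015 needs D = 0.015 / 0.7 = 0.021.
- *With 3% lost before month 12 and a base rate of 5%:* complete-case means -0.300, -0.295, -0.289 and -0.273 at log-odds 0, 0.7, 1.2 and 1.8.
- *The same with a base rate of 10%:* -0.302, -0.293, -0.284 and -0.265. At 12-18% loss the bias is thus small for weak dependence and about 0.03 (at most 0.035) for the strongest.
- *Two-visit likelihood model:* -0.299 to -0.303 throughout these eight scenarios.

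The standard error is sqrt(2 x 0.8^2 / 228) = 0.075 at 5% loss (228 = 0.95 x 240 per arm). A bias of 0.015 is 0.20 of that. At 17% loss (about 199 per arm) it is sqrt(1.28 / 199) = 0.080, and 0.03 is 0.38 of that.

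A repeat with independent code agreed with these ranges.

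**5. A harsher mechanism.** Assume a true difference of -0.40 and SD 0.8, with 90% of participants above a cut-off in 12-month HbA1c lost. Bias toward zero is then 0.02-0.04 at about 5% loss, 0.035-0.085 at 10% and 0.05-0.14 at 20%. The two-visit model is off by 0.006 at most.

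**6. Precision under random loss.** The proportional variance reduction from adding the 12-month value is about rho^2 x f, where f is the share with a 12-month but no 24-month value. With rho = 0.7: 0.49 x 0.05 = 2.5%, and 0.49 x 0.10 = 4.9%.

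**The case against.** **The plan already has MMRM.** The carry-over sentence brings both MMRM mentions with it, and the first is aimed at missing data without naming visits. A 12-month value could be included there. This stands: a reader might infer that the plan has no answer to missing data for these variables, and that would be wrong. But MMRM remains a sensitivity analysis, and the only time points stated for it are baseline and 24 months.

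**These variables may not be secondary endpoints.** The numbered list in Study endpoints does not include them. They follow in a separate sentence, which does not name HbA1c or pulse rate. This stands as a real ambiguity, so the point depends on how that sentence is read. In favour of the wider reading, the Abstract counts metabolic parameters among the key secondary endpoints. Also, Measurements gives HbA1c as the only blood test taken at 12 months, so it is the natural content of the 12-month laboratory data.

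**The 12-month data are not discarded.** Correct. A reader might infer that they are never analysed, but Study endpoints has them evaluated in their own right. Only the 24-month comparison fails to use them.

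**The mechanism is uncertain.** Treatment may be intensified in either arm when the glycaemic goal is missed, so poor 12-month control need not lead to loss. Table 2 does list seriously poor control as a reason for discontinuation, but at HbA1c 12.0% or more against entry below 10.0%, so it may be rare. A triggering value between scheduled visits would also be absent from a two-visit model. All this stands and limits the size of the point.

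**It is a matter for the SAP.** Modelling detail is indeed often left there. Here, however, the article states a rule for the secondary analysis, and that rule fits these variables less well than IMT.

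**Conclusion.** The point holds as a minor, inexpensive improvement. On the reading that these variables fall under the secondary analysis, the stated main method for their 24-month comparison leaves out usable data. It is open to bias if loss after month 12 depends on the 12-month value.

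Under the graded-dependence assumptions the bias is modest: about 0 to 0.015 HbA1c points near the planned loss and about 0.03 with strong dependence at 12-18% loss, for an assumed true difference of -0.30. Only a steep cut-off mechanism, or loss of two to four times the plan, makes it larger. The direction toward zero follows from assuming that poor 12-month control raises the chance of loss. Another pattern of loss could act differently.

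A reader might go further and infer that the HbA1c result will be biased, that a false benefit could arise, or that the trial's main conclusion is at risk. The documents support none of these. Bias is conditional on the loss mechanism, in the simulated cases it works against ipragliflozin, and the primary endpoint and sample size are untouched. If loss is purely random, the cost is at most a few percent of variance.

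**What to change.** Add one sentence to the analysis plan, which the article says is still to be developed. For variables measured at both 12 and 24 months (HbA1c, blood pressure, pulse rate, body weight, BMI), the main analysis is an MMRM of the 12- and 24-month changes. It has treatment, visit, treatment-by-visit, baseline value and the allocation factors, with an unstructured covariance. Report the 24-month and 12-month treatment contrasts from it. Keep the complete-case ANCOVA at 24 months as a supporting analysis, and leave the IMT analysis unchanged. The same sentence should say whether these variables belong to the secondary analysis.

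The cost is small: no new visits, data or participants. These variables would no longer share the IMT model. The result would still be valid only if loss depends on observed values, an assumption that should be stated.

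### The P<0.05 significance rule covers primary and secondary comparisons alike, with no testing order and no nominal label, so secondary IMT claims have no error control

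*Protocol article*

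**What the plan says.** Study endpoints names one primary variable: "The primary endpoint in the study is the change in mean IMT of the CCA from baseline to 24 months". It then states: "The secondary endpoints are the values and changes in parameters after 24 months of treatment". Eight numbered groups follow. The first four are IMT summaries other than the primary. The rest cover biomarkers, functional tests, abdominal fat measures and urinary albumin. A further sentence adds blood pressure, weight, BMI and laboratory data at 12 and 24 months. The Abstract counts other carotid IMT parameters among the key secondary endpoints.

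The Statistical analysis plan section gives the primary analysis as a baseline-adjusted ANCOVA of the change, adjusted for the allocation factors, and continues: "The secondary analysis will be performed in the same manner as the primary analysis". Its last paragraph starts with "All comparisons are planned and all" P values are two-sided, and then sets the rule that P "values <0.05 will be considered statistically significant". The section contains no hierarchy, no division of alpha, and no label separating confirmatory from exploratory results. It says that a statistical analysis plan will be written before recruitment is complete and the database is locked.

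**The concern.** Taken literally, the rule lets any secondary comparison be called statistically significant on the same terms as the primary one. This matters most for IMT. Study overview and design frames the hypothesis broadly, as slower progression of carotid atherosclerosis, so a P value below 0.05 for bulb, ICA or maximum IMT would read as support for it even if mean CCA-IMT showed nothing. At stake is whether an anti-atherosclerotic effect can be claimed from a secondary IMT variable after a null primary test, with no bound on how often that happens by chance.

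**Working it through.** **The plan's own figure.** Sample size estimation gives 222 per arm for a difference of 0.016 mm, SD 0.06 mm, two-sided 5%, 80% power. The normal formula is n = 2(SD/difference)²(1.960 + 0.842)² = 2 × 14.06 × 7.85 = 220.7, so 221. The t-test version gives 222 (power 80.05%), so the figure is reproduced. It concerns the primary variable only. The article gives no such calculation for any secondary endpoint and no familywise error rate.

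**Secondary IMT family.** Study endpoints, groups 1 to 4, yields 7 variables: mean IMT of bulb and ICA (2), maximum IMT of CCA, bulb and ICA (3), the overall mean of the site means (1), and the mean of the site maxima (1).

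If all are null and independent, P(at least one P<0.05) = 1 − 0.95^7 = 30.2%.

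Independence cannot hold exactly, because two of the seven are averages of site values. I therefore simulated null test statistics (1,000,000 draws per row) for mean and maximum IMT at three sites. For one measure, the correlation between sites is b. At one site, the correlation between mean and maximum is m. Across both it is b × m. The two summary variables are equal-weight averages. The article gives no correlations, so b and m are assumptions.

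| b | m | At least one of 7 at P<0.05 | Same, with primary non-significant | Same, favouring ipragliflozin |
|---|---|---|---|---|
| 0 | 0.6 | 24.3% | 21.8% | 11.2% |
| 0 | 0.8 | 22.2% | 19.1% | 9.8% |
| 0.3 | 0.7 | 21.1% | 18.1% | 9.1% |
| 0.6 | 0.6 | 18.6% | 15.3% | 7.7% |
| 0.6 | 0.8 | 16.9% | 13.2% | 6.6% |

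For comparison, the chance of a false primary result favouring ipragliflozin is 2.5%.

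**All named secondary tests.** From Study endpoints and Measurements:

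- numbered groups: 7 IMT + 4 biomarkers + 5 functional tests (echocardiography counted once) + 3 waist and fat + 1 urinary albumin = 20;
- systolic BP, diastolic BP, weight and BMI at two times: 8, total 28 (this assumes BP is tested as two variables);
- HbA1c at two times: 2, total 30.

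The rest of the laboratory panel (Additional file 2) is not counted, and the full list of functional tests (Additional file 3) is not shown. Value and change are counted once.

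Under a global null:

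- 20 independent tests: 1 − 0.95^20 = 64.2%, expected false positives 20 × 0.05 = 1.0;
- 30 independent tests: 1 − 0.95^30 = 78.5%, expected false positives 30 × 0.05 = 1.5;
- 30 tests with strong correlation within families and little between them (simulated, assumed): about 60-69%;
- 22 non-optional tests (7 IMT, 4 biomarkers, 5 waist/weight/BMI, 4 BP, 2 HbA1c) in the same kind of blocks: about 56%.

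With 30 tests, the figure falls to about 50% only if all of them share a correlation of about 0.5, which is implausible across measures as different as hsCRP, FMD, BP and IMT.

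**The case against.** The strongest reply is that the article is a summary. It describes the analysis briefly and defers to an analysis plan still to be written, where multiplicity and the labelling of secondary endpoints are usually settled. A bare threshold sentence does not say that no adjustment will be made. Leaving secondary endpoints unadjusted is also common in an investigator-initiated mechanistic trial. This reply stands in part: silence alone would be no finding. But the article is not silent. It states a rule, ties it to all comparisons, and has secondary endpoints analysed like the primary, so the later plan has to narrow a rule already published.

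Several stronger readings are tempting, and the document does not support them:

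- A reader might infer that the trial's main error rate is inflated. It is not. There is one primary variable, one time point and one contrast, and the sample size is built on it.
- A reader might infer that the investigators intend to replace a null primary with a secondary result. Nothing in the article plans this; the wording only fails to prevent it.
- A reader might take 79% as the chance of a spurious finding in this trial. That figure needs 30 independent, truly null tests. The Background reports that ipragliflozin improves glycaemic control, BP, weight and visceral fat, which covers 11 of the 30 (8 + 2 + 1). The other 19 give 1 − 0.95^19 = 62% if independent, with 0.95 expected false positives. At least seven of the 30 (five functional tests, two CT fat measures) are also optional.
- A reader might infer that listing both values and changes doubles the tests. With baseline as a covariate, both give the same treatment contrast, so no error is added.

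**Conclusion.** The point holds for secondary claims only. The article sets one significance threshold for primary and secondary comparisons, without an order or a nominal label. The seven alternative IMT summaries carry the main risk. With no true effect, 17-24% of trials (30% if independent) would have at least one at P<0.05. In about 13-22% this would accompany a non-significant primary, and in about 7-11% it would favour ipragliflozin. These ranges rest on assumed correlations (between sites 0-0.6, mean with maximum 0.6-0.8). Across roughly 20-30 named secondary tests the benchmark is about 55-79%; it rests on a global null, on the correlation assumed, and on a count that depends on Additional files not shown. The threshold is a decision rule, so none of this means that secondary results will be significant. The validity of the primary analysis is not in question, but what the trial may conclude from its secondary endpoints is, and the wording should be corrected.

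**What to change.** State in the analysis plan, before database lock, that confirmatory statistical significance applies only to the primary test, the change in mean CCA-IMT at 24 months. Report every secondary endpoint with its estimate, 95% CI and a nominal P value labelled exploratory.

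Optionally, if confirmatory claims on secondary IMT variables are wanted, test the seven only after a significant primary result, by Holm's procedure or in a fixed, pre-stated order.

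The cost is a few sentences. Sample size, data collection and the power of the primary test do not change. The downside is fewer significance claims for secondary endpoints.
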